
### Participant timeline

The participant timeline is based on the SPIRIT statement and is provided in Table 1.

**Table 1 Tab1:**
[figure not shown]
SPIRIT figure: time points for enrolment, interventions, and assessment

SPADI, Shoulder Pain and Disability Index; NPRS, Numerical Pain Rating Scale; ROM, Range of motion; IL-6, Interleukin 6; HADS, Hospital Depression and Anxiety Scale; SF-36, 36-item short-form health survey

### Sample size estimation

To our knowledge, no trial could be found evaluating the comparative effects of LLLT and MET among diabetic patients with frozen shoulder. However, given that the minimal clinically important difference (MCID) of the SPADI has been reported to be 8.0% points [67], the required sample size was estimated to detect a minimum difference of 8.0% (standard deviation [SD] = 10.0%) points in SPADI between the experimental groups (LLLT and MET) and control group (CTE) means post-intervention. Using the following parameters: F-test, repeated measures, between-subjects analysis of variance (ANOVA); alpha (*α*) level of 0.05; power of 0.80; effect size of 0.38 when accounting for 3 repeated measures; and correlation among repeated measures of 0.5, a total of 48 participants (16 participants per group) will be required for the trial. While anticipating an attrition rate of 25% (*n* = 12), the final sample size is 60, with 20 participants per group. Calculations were carried out using G Power 3.1.9.2 software [68].

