### Plans for assessment and collection of outcomes

All outcome measures will be collected at inclusion (baseline), at post 8-week intervention, and 3 months follow-up (Table 1).

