### Statistical methods for primary and secondary outcomes

The intention-to-treat principle will be the main analysis and will be conducted by including each participant's available data according to original allocation and irrespective of the level of attendance. A mixed between–within subjects ANOVA will be used to evaluate time effect (baseline, 8 weeks, 3 months), group effect (LLLT group, MET group, control group), and group-by-time interaction effect for all outcome measures. Post hoc analysis using Bonferonni correction will be applied for pairwise comparisons for significant differences detected in the primary outcome measures. Fisher's least significant difference (equivalent to no adjustment) will be applied to the secondary outcome measures. Effect size will be computed to describe the magnitude of change in all the outcomes. Potential confounding variables such as age, gender, BMI, and duration of DM will be controlled in the main analyses.

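### The stated 80% power applies a single-visit effect size to an average of three visits, one of which precedes randomisation; the planned group comparisons have less power under the plan's own 8-point target

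*Protocol article*

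**What the plan says.** The Sample size estimation section sets the target: the trial is sized "to detect a minimum difference of 8.0% (standard deviation [SD] = 10.0%) points in SPADI between the experimental groups (LLLT and MET) and control group", and the difference is described as post-intervention. The test is named as "F-test, repeated measures, between-subjects analysis of variance (ANOVA"), with an alpha "level of 0.05; power of 0.80". The remaining inputs and the result are "effect size of 0.38 when accounting for 3 repeated measures; and correlation among repeated measures of 0.5, a total of 48 participants". The total is then raised for drop-out: "While anticipating an attrition rate of 25% (*n* = 12), the final sample size is 60, with 20 participants per group".

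The only three measurements in the trial are listed under Plans for assessment and collection of outcomes: "All outcome measures will be collected at inclusion (baseline), at post 8-week intervention, and 3 months follow-up". The Outcomes section places the first assessment before randomisation.

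The primary analysis, under Statistical methods for primary and secondary outcomes, is a mixed ANOVA that tests "time effect (baseline, 8 weeks, 3 months), group effect (LLLT group, MET group, control group), and group-by-time interaction effect". It continues: "Post hoc analysis using Bonferonni correction will be applied for pairwise comparisons for significant differences detected in the primary outcome measures".

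**The concern.** The sample size section describes 0.38 as already allowing for the three measurements. It does not: it is the one-visit effect size. Entering it in the between-subjects repeated-measures test with three measurements treats an 8-point gap as the average over all three. The stated 8 points is a post-treatment difference, and randomisation makes the expected gap at baseline zero. The average gap is therefore smaller than the calculation needs, unless the follow-up effect is well above the stated target.

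The section also presents the total as enough to detect the difference between the experimental arms and control. Whether LLLT or MET beats CTE is settled by Bonferroni-adjusted pairs, which the calculation does not address.

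At stake is how the result will be read. If the trial is believed to have 80% power, a non-significant comparison on SPADI could be taken as fair evidence of no benefit, when the chance of detecting the target difference may have been near or below one half.

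**Working it through.** **Inputs from the protocol article.** Difference 8, SD 10, alpha 0.05, f = 0.38, m = 3 measurements, rho = 0.5, N = 48 before attrition and 60 after (Sample size estimation); k = 3 equal groups (Randomisation section); visits at baseline, 8 weeks and 3 months.

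**Assumptions added here.** Equal variances and correlations across visits, and a stated pattern of group differences over the three visits. The main pattern is 0, 8, 8. The plan gives no size for the 3-month effect.

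**1. Where 0.38 comes from.** Group means 0, 8, 8 have mean 5.33 and standard deviation √[(5.33² + 2.67² + 2.67²)/3] = 3.77. So f = 3.77/10 = 0.377, which rounds to 0.38. No repeated measurement enters.

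**2. Reproducing the plan's figure.** For the between-subjects test, λ = f²·N·m / [1 + (m − 1)·rho] = 0.38² × 48 × 3 / 2 = 10.40. With 2 and 45 degrees of freedom, power is 0.804. The stated 48 is reproduced.

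**3. Group effect with no baseline difference.** Under 0, 8, 8 the three-visit mean differs by (0 + 8 + 8)/3 = 5.33 points, so f falls to 0.377 × 2/3 = 0.251. Then λ = 0.251² × 48 × 3 / 2 = 4.55 and power is 0.44. Reaching 0.80 would take 105 completers.

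**4. Group-by-time interaction.** The squared interaction deviations over the nine cells sum to 28.44. The error variance is 100 × (1 − 0.5) = 50. With 16 per group, λ = 16 × 28.44 / 50 = 9.10. With 4 and 90 degrees of freedom, power is 0.64.

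**5. One Bonferroni pair.** Alpha is 0.05/3 = 0.0167.
- At week 8: d = 8/10 = 0.80, noncentrality 0.80 × √(16/2) = 2.26, 45 degrees of freedom, power 0.42.
- On the three-visit marginal mean: the variance is 100 × (1 + 2 × 0.5)/3 = 66.7, so d = 5.33/8.16 = 0.65 and power is 0.27.

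**6. Summary under 0, 8, 8.**

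| Test | N = 48 | N = 60 (no loss) |
|---|---|---|
| Group effect | 0.44 | 0.54 |
| Group-by-time interaction | 0.64 | 0.76 |
| Bonferroni pair, week 8 | 0.42 | 0.53 |
| Bonferroni pair, marginal means | 0.27 | 0.35 |

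**7. Sensitivity to the 3-month effect, N = 48.**

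| Differences at baseline, 8 weeks, 3 months | Group effect | Interaction |
|---|---|---|
| 0, 8, 8 | 0.44 | 0.64 |
| 0, 8, 4 | 0.26 | 0.50 |
| 0, 8, 0 | 0.14 | 0.64 |

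The week-8 pair stays at 0.42 in all three rows, because it uses only that visit.

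**8. Baseline SPADI as covariate, week 8.** The residual variance falls by the factor 1 − 0.5² = 0.75. The omnibus λ is 48 × 0.377² / 0.75 = 9.10; with 2 and 44 degrees of freedom, power is 0.75. For a Bonferroni pair, d = 0.80/√0.75 = 0.92 and power is 0.55. With 60 completers these are 0.84 and 0.67.

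**The case against.** The arithmetic is correct for the test that the section names, as step 2 shows. That stands: nothing was miscalculated. The fault lies in matching that effect size to those three visits.

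A reader might infer that the calculation requires the full 8-point gap to be present at baseline. It does not, strictly. It requires a gap averaging 8 points over the three visits, and differences of 0, 12, 12 would also satisfy it (0.80 at N = 48). The plan gives no such pattern, however. It states an 8-point post-intervention difference, so this route does not rescue the stated power.

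A reader might also take 42% to 64% as a fixed property of the trial. The documents do not support that. The group-effect and interaction figures depend on a 3-month effect that the plan leaves unstated: power is lower if the gap fades to 4 points, and the interaction would reach 0.89 if the gap grew to 12 points at 3 months. The analysis section also does not say whether pairs are compared by visit or on marginal means, and the marginal-means figure lies below that range.

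It is common to power the omnibus test rather than each post hoc pair, and that is fair. But both omnibus tests between groups fall short here as well.

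Finally, 48 is the number left after drop-out, while the main analysis uses all available data and imputation is planned. Even with all 60 complete, no figure under 0, 8, 8 reaches 0.80.

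**Conclusion.** The concern holds in conditional form. The 80% is reproducible, but only by giving the average of three visits an effect size that belongs to one post-treatment visit, although one of the three is measured before randomisation. The statement that 0.38 allows for the repeated measurements is wrong.

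Under SD 10, rho 0.5, equal correlations and an 8-point gap held at 3 months, the planned group comparisons have 0.27 to 0.64 power at 48 participants and 0.35 to 0.76 at 60, depending on the test. The week-8 pairwise figures (0.42 and 0.53) do not depend on the 3-month effect or on rho; the others do. No source or range is given for the correlation of 0.5.

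**What to change.** No additional participants are needed.

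1. In Sample size estimation, delete the wording that says the effect size allows for the three measurements. Restate power for the test that will decide the primary outcome, both omnibus and for a Bonferroni pair. State the assumed 3-month difference and the correlation alongside, and say whether pairs are compared at a visit or on marginal means.

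2. Preferably, before any unblinded analysis, revise the statistical methods section and the sample size section together, so that follow-up SPADI is analysed with baseline SPADI as a covariate instead of as a level of the time factor. The covariates now named are age, gender, BMI and duration of DM, so baseline SPADI would be an addition. Changing only the sample size section would put a new mismatch in place of the present one.

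The second step raises week-8 power at 48 participants to about 0.75 omnibus and 0.55 pairwise at rho 0.5, still short of 0.80. The cost is a less favourable stated power and a small change to the primary analysis model, handled as a protocol amendment.

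### The 25% attrition allowance was added to 48 rather than divided out, so 60 randomised leaves 45 completers, short of the plan's own required 48

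*Protocol article*

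**What the plan says.** Under *Sample size estimation*, the protocol article bases the calculation on a between-group difference in SPADI: "to detect a minimum difference of 8.0% (standard deviation [SD] = 10.0%) points in SPADI". The test is specified as "F-test, repeated measures, between-subjects analysis of variance (ANOVA"), with "level of 0.05; power of 0.80", an "effect size of 0.38 when accounting for 3 repeated measures", and a correlation of 0.5 among the repeated measures. From these inputs it concludes that "a total of 48 participants (16 participants per group) will be required for the trial".

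It then allows for dropout. The sentence opens "While anticipating an attrition rate of 25"%, gives the corresponding count as n = 12, and ends with the statement that "the final sample size is 60, with 20 participants per group". The abstract repeats the total of sixty, and the randomisation section confirms 1:1:1 allocation.

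**The concern.** An attrition rate is normally the share of enrolled participants who are lost. The number to randomise is then the required number divided by the share expected to remain. The plan instead took 25% of the number that must remain and added it on. That gives too small a total, because the 25% loss will also fall on the added participants.

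At stake is the power statement for the primary outcome. The section presents 60 as enough to keep 48 evaluable participants, and so 80% power, at the attrition it expects. If that attrition occurs, the trial falls below its own requirement although the protocol says the loss was allowed for. A null result would then be read against a power claim that did not hold.

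**Working it through.** **Inputs, all from *Sample size estimation*:** k = 3 groups, m = 3 measurements, correlation ρ = 0.5, effect size f = 0.38, α = 0.05, target power 0.80, required N = 48, attrition d = 25% (given as 12), final N = 60.

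**Step 1: reproduce the required 48.** For the between-groups F-test in a repeated-measures ANOVA, the noncentrality parameter is

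λ = f² · N · m / (1 + (m − 1)ρ), with degrees of freedom k − 1 and N − k.

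Here f² = 0.1444 and m / (1 + 2 × 0.5) = 1.5, so λ = 0.2166 · N.

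| N | λ | Power |
|---|---|---|
| 45 | 9.75 | 0.774 |
| 47 | 10.18 | 0.794 |
| 48 | 10.40 | 0.804 |
| 60 | 13.00 | 0.892 |

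The smallest N with power of at least 0.80 is 48, so the plan's base figure reproduces. It has no slack: one participant fewer already falls below 0.80.

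**Step 2: reproduce the 60.** 0.25 × 48 = 12, and 48 + 12 = 48 × 1.25 = 60. This matches the stated count of 12 and the stated total, so this is how the allowance was built.

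**Step 3: apply the stated attrition to the stated total.**
- 25% of 60 is 15, and 60 − 15 = 45.
- If losses are even across arms, 20 × 0.75 = 15 per group, against 16 required.
- The shortfall is 48 − 45 = 3 participants.
- From Step 1, power at 45 is 0.774, against 0.804 at 48.

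**Step 4: find the attrition that 60 does cover.** 1 − 48/60 = 0.20, and 12/60 = 20%. The count of 12 is therefore consistent with 60 only at a 20% rate.

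**Step 5: find the total that 25% attrition would need.** N = 48 / (1 − 0.25) = 64. With equal arms, 16 / 0.75 = 21.3, rounded up to 22 per arm, which makes 66.

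**The case against.** The arithmetic is hard to dispute. The case on the other side concerns how much it matters.

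- **Partial data count.** The protocol says that data collected up to withdrawal will be used, that the main intention-to-treat analysis takes each participant's available data, and that multiple imputation by chained equations will handle missing values. Someone lost between week 8 and the 3-month visit still has a week-8 SPADI score. The 0.774 therefore assumes that every lost participant contributes nothing. Actual power at 25% attrition may lie between that and the 0.892 for 60 complete participants. This stands as a limit on the practical loss. It does not rescue the calculation: the allowance was there to leave 48 after attrition, and imputation cannot fully restore outcomes that were never observed. The per-protocol sensitivity analysis, restricted to participants with complete data, gets no such relief.
- **The effect is small.** Three participants and about 3 percentage points of power are less than the uncertainty in the assumed SD, correlation and attrition rate. Nothing is biased, and at 20% attrition or below the target is met. This is fair, but the figure is still wrong by the plan's own inputs and is not a matter of judgement.
- **The working is visible.** Because n = 12 is printed beside 48 and 60, the 25% could be read as a loosely labelled top-up. But the text calls it an attrition rate, and readers will take it as one.
- **It is late to change the size.** *Trial status* gives recruitment as open since February 2023 and expected to end by May 2024; the article appeared on 30 April 2024. This argues for correcting the statement rather than the number.

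**Conclusion.** The concern holds. The stated 25% attrition, the count of 12 and the total of 60 are mutually inconsistent. At 25% attrition, 60 randomised leaves 45, three below the plan's required 48. Under the plan's own formula and inputs, power falls from 0.804 to 0.774, just under the stated 0.80.

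The power figure assumes that attrition reaches the full 25% and that lost participants add no information. The figure of 15 per group further assumes even losses across arms. The inconsistency itself needs none of these assumptions. It is a definite error in the justification of the primary sample size, with a modest effect on the trial.

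**What to change.** Keep 60 and correct the sentence in *Sample size estimation*, for example:

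> With 60 participants randomised (20 per group), up to 20% attrition (n = 12) leaves the required 48. At 25% attrition, 45 would remain and power under the same assumptions would be about 77%.

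If the 25% allowance with full power is to be kept instead, the stated total should be 64, or 66 (22 per group) for equal arms. With recruitment close to its planned end, that is the less practical route.

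The restatement costs one sentence and a slightly less favourable power figure. It changes nothing in recruitment, treatment or analysis.

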### Recruitment

Diabetic patients with shoulder pain at ABUTH, Zaria will be recruited from the endocrine clinic or general outpatient department upon referral by a consultant endocrinologist or general practitioner for physiotherapy. Recruitment will be through adverts posted on clinic notice boards. Eligibility will be determined by an experienced musculoskeletal physiotherapist using standardised clinical diagnosis, including inspection, palpation, and examination of ROM and provocative maneuvers. Written informed consent will be obtained from eligible participants by the physiotherapist after explaining the study procedure.

### Randomisation: sequence generation, allocation concealment and blinding

Eligible participants who provide consent for participation will be randomly assigned to LLLT group, MET group, or control group with an allocation ratio of 1:1:1 using block randomisation procedure. To achieve balance in the allocation of participants to the three treatment arms, a block randomisation sequence with variable block sizes will be generated using computed-generated random numbers. No stratification will be used. The allocation sequence will be concealed using consecutive numbered, sealed, and opaque envelopes. The block sizes and randomisation list will be concealed until the end of the study. An independent physiotherapist at the Department of Physiotherapy, ABUTH, Zaria, who will not be involved in any other aspects of the study will be responsible for the allocation of participants to the various study arms. Physiotherapists undertaking outcome assessments and statistician performing data analyses will be blinded to group allocation.

### Procedure for unblinding if needed

Due to the nature of the exercise intervention in this study, neither participants nor treatment providers will be blinded. However, participants will be informed about their group allocation after the study is completed.

### Plans for assessment and collection of outcomes

All outcome measures will be collected at inclusion (baseline), at post 8-week intervention, and 3 months follow-up (Table 1).

### Plans to promote participant retention and complete follow-up

To minimise loss from follow-up, participants' contact information will be validated at each time point. They will be reminded of their follow-ups through phone calls at regular intervals.

### Data management

Participants' data will be stored in a logbook and electronically using Microsoft Excel sheets on a computer hard drive. The data will be checked for errors before entry.

### Confidentiality

All participants will be recognised only by their ID codes and their information will be kept strictly confidential, and only accessed by members of the trial team or ethics committee. Open request, only anonymised data will be made available to other researchers to enable international prospective analyses.

### Plans for collection, laboratory evaluation, and storage of biological specimens for genetic or molecular analysis in this trial/future use

This is not applicable as no biological specimens will be collected.

### Statistical analysis

All statistical procedures will be conducted using SPSS version 24.0 (IBM Co., Armonk, NY, USA) at a probability level of 0.05. Data distribution will be examined statistically using the Kolmogorov–Smirnov and Shapiro–Wilk test, and graphically using histograms, Q-Q plots, and Boxplots. The Levene test will be applied to check for homogeneity of variance. In case of skewed distribution, data transformations using log or square root transformation will be used. Continuous variables will be presented by mean and SD whereas categorical variables will be presented using frequency and percentage. Baseline comparison of continuous variables among the groups will be performed using One-way ANOVA and for categorical variables using the chi-square (χ^2^) test.

### Statistical methods for primary and secondary outcomes

The intention-to-treat principle will be the main analysis and will be conducted by including each participant's available data according to original allocation and irrespective of the level of attendance. A mixed between–within subjects ANOVA will be used to evaluate time effect (baseline, 8 weeks, 3 months), group effect (LLLT group, MET group, control group), and group-by-time interaction effect for all outcome measures. Post hoc analysis using Bonferonni correction will be applied for pairwise comparisons for significant differences detected in the primary outcome measures. Fisher's least significant difference (equivalent to no adjustment) will be applied to the secondary outcome measures. Effect size will be computed to describe the magnitude of change in all the outcomes. Potential confounding variables such as age, gender, BMI, and duration of DM will be controlled in the main analyses.

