
### Criteria for discontinuing or modifying allocated interventions

No provisions for changing the trial arm allocation. However, the criteria for discontinuing the allocated interventions will be participant withdrawal of consent at any point of the study without providing reasons and participant experiencing worsening of condition related to other diabetic complications. Any data collected up to the point of withdrawal will be included in the study and intention-to-treat analyses will be conducted.

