### Methods in analysis to handle protocol non-adherence and any statistical methods to handle missing data

As sensitivity analyses, per-protocol analyses will be conducted using data from participants with fully available data and no protocol violations. The per-protocol dataset will be predefined in the statistical analysis plan of the study. Multiple imputations by chained equations [69] will be used to handle missing data.

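### The main analysis promises intention-to-treat on available data but names a three-visit ANOVA that drops anyone missing a visit, and the plan does not say whether multiple imputation feeds it

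*Protocol article*

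**What the plan says.** Four statements in the protocol article bear on this point.

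- **Analysis set** (Statistical methods for primary and secondary outcomes). Intention-to-treat is the main analysis, to be done on each participant's "available data according to original allocation and irrespective of the level of attendance".
- **Method** (same section, next sentence). "A mixed between–within subjects ANOVA will be used to evaluate time effect (baseline, 8 weeks, 3 months"), along with the group effect and the group-by-time interaction, for every outcome. Imputation is not mentioned in this section.
- **Missing data** (Methods in analysis to handle protocol non-adherence and any statistical methods to handle missing data). The section begins "As sensitivity analyses, per-protocol analyses will be conducted using data from participants with fully available data and no protocol violations". It then refers the per-protocol dataset to a statistical analysis plan and closes with "Multiple imputations by chained equations [69] will be used to handle missing data". The analysis that the imputed data will serve is not named.
- **Withdrawals** (Criteria for discontinuing or modifying allocated interventions). "Any data collected up to the point of withdrawal will be included in the study and intention-to-treat analyses will be conducted".

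The Statistical analysis section names the software: "All statistical procedures will be conducted using SPSS version 24.0".

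**The concern.** A classical mixed between–within ANOVA needs all the repeated measurements from each participant it includes. With three time points, someone who has baseline and 8-week SPADI but no 3-month value is left out altogether, and the observed 8-week score goes with them. On observed data, the named method therefore cannot keep the promise to use each participant's available data.

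Imputation could repair this, but the section that defines the main analysis does not mention it, and the section that introduces it does not link it to the main ANOVA. Two competent analysts could follow this text and report different primary results, one from completers and one from imputed data.

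Three things are at stake: precision, because observed data are discarded; possible bias, if those who leave differ by arm in a way related to outcome; and a choice between two primary results that could be made after the data are seen.

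**Working it through.** **Inputs** (Sample size estimation): difference 8.0 points, SD 10.0, alpha 0.05, power 0.80, effect size f = 0.38, m = 3 measures, correlation ρ = 0.5, k = 3 groups, 48 evaluable participants, attrition 25% given as n = 12, final size 60.

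**Step 1: reproduce the plan's figure.** Group means of 8, 8 and 0 have a grand mean of 5.33. Their standard deviation is √[(2 × 2.67² + 5.33²)/3] = 3.77, so f = 3.77/10 = 0.377, in line with 0.38. For the between-groups test in a repeated-measures ANOVA:

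λ = f² × N × m / [1 + (m − 1)ρ] = 0.1444 × N × 3 / 2 = 0.2166 N, with k − 1 = 2 and N − 3 degrees of freedom.

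At N = 48, λ = 10.40 and the power from the noncentral F distribution is 0.804. The stated 48 reproduces, and it is a count of participants with complete data.

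**Step 2: how many a completer analysis would drop.** The stated loss of 12 is 25% of 48 but 12/60 = 20% of those randomised. A loss of 25% of 60 is 15. If each lost participant misses at least one visit, the ANOVA on observed data omits 12 to 15 people and keeps 48 to 45.

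**Step 3: power with the plan's own test.**

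| Participants analysed | λ | Power |
|---|---|---|
| 45 (25% of 60 lost) | 9.75 | 0.774 |
| 48 (12 lost) | 10.40 | 0.804 |
| 60 (none lost) | 13.00 | 0.892 |

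The last row is an upper bound. Imputation or a mixed model recovers only part of the gap, because data that were never observed carry no information of their own.

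**Step 4: bias, as an illustration only.** Assumptions: true 8-week difference 8.0, SD 10, correlation 0.5, 25% lost after week 8, and log-odds of loss rising by 0.5 to 1.0 per SD of worse 8-week SPADI where loss is outcome-related.

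| Dropout mechanism | Completer 8-week difference |
|---|---|
| Same relation within each arm | 8.0 (no bias) |
| Depends on absolute score, same rule in all arms | about 6.9 to 7.6 |
| Outcome-related in control only, random in the active arm | 5.9 to 6.8 |

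In the last row the bias is towards no difference, by 8.0 − 6.8 = 1.2 to 8.0 − 5.9 = 2.1 points. If the asymmetry were reversed, the same shifts would exaggerate the effect, to 9.2 to 10.1. The documents do not say which pattern to expect.

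**The case against.** The strongest reply is that the missing-data section already answers the point. Its imputation sentence carries no restriction, and the phrase about sensitivity analyses belongs to the per-protocol sentence, with another sentence in between. The section also places the fully-available-data analysis among the sensitivity analyses, which suggests that the main analysis is not meant to be confined to completers. Multiple imputation uses every observed value, so it need not conflict with the available-data wording. Pooling details are commonly left to the statistical analysis plan.

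Much of this stands. A reader might infer that the main result simply is a completer analysis. The text does not support that: if imputation feeds the ANOVA, nobody is dropped. The absence of imputation details is also no fault in an article. What the reply does not remove is that the method named for the main analysis cannot by itself deliver the property claimed for it, and that no sentence joins the imputation to it.

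Two other inferences should not be drawn. First, the discontinuation section says that data up to withdrawal are kept. It does not say that assessments stop when treatment stops, and the worsening it mentions relates to other diabetic complications, not to the shoulder. Second, no passage supports outcome-related loss in the control arm alone. Participants are unblinded, so differential loss is possible, but the 5.9 to 6.8 range is one chosen scenario.

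**Conclusion.** The point holds in a conditional form. The stated analysis set and the named ANOVA do not fit together on observed data, and the planned imputation is not tied to the main analysis. Unless it feeds the ANOVA, the primary result would be a completer analysis labelled intention-to-treat, with 12 to 15 of 60 participants omitted and power of about 0.80 to 0.77 against at most 0.89. These figures rest on the plan's f = 0.38 and ρ = 0.5, and on each lost participant missing at least one visit. Even with 12 lost, power stays at the planned 0.80, so the loss is of recoverable precision and not a failure of the design. Bias depends on dropout that is both outcome-related and different between arms; it is nil if the relation is the same within each arm. This should be corrected, since a better method is available in the named software at almost no cost.

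**What to change.** **Preferred.** In Statistical methods for primary and secondary outcomes, replace the ANOVA as main analysis with a likelihood-based linear mixed model for repeated measures: 8-week and 3-month SPADI as outcomes, group, time and their interaction as factors, baseline SPADI as covariate, unstructured covariance, fitted by REML. SPSS MIXED does this. It uses every observed post-baseline visit under missing-at-random, so a participant with only an 8-week value still counts. State that multiple imputation is a sensitivity analysis.

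**Alternative, if the ANOVA is kept.** State in the same section that multiply imputed data feed the main intention-to-treat ANOVA, and how the F tests and pairwise comparisons are pooled across imputations.

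**Cost.** A few sentences of analysis text and slightly more analysis work, with no change to randomisation, sample size or visits. Both routes rely on missing-at-random, and the text should say so. The choice should be fixed before the unblinded data are analysed.
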